#### Group-level analysis

All statistical analyses will be performed using SPSS software (SPSS 25.0, SPSS Inc., Chicago, Illinois). The intention-to-treat principle will be used for the analysis of functional and electrophysiological data. One-way analysis of variance (ANOVA) will be used to compare the demographic characteristics and baseline assessment (T0) of all outcomes among groups. To compare the treatment effects of different rTMS protocol, a two-way mixed design ANOVA with between-subject factor “Group” and within-subject factor “Time” will be performed for the clinical and electrophysiological changes. Moreover, Bonferroni correction will be employed for post hoc multiple comparisons. *P* < 0.05 will be considered statistically significant for all analyses.

For rs-fMRI and DTI data, a two-way mixed design ANOVA will be performed, with between-subject factor “Group” and within-subject factor “Time” on the data generated in the data processing step, including Eg, El, network betweenness, clustering coefficient, and FA AI. For tb-fMRI data, a whole brain paired T-test will be performed between the task state blocks and baseline blocks in the FC group, and the voxels whose t value is higher than the threshold will be regarded as the activated brain region. For cM1-LF, cPMd-HF, and CON groups, a two-way mixed design ANOVA, with between-subject factor “Group” and within-subject factor “Time” will be performed within the former activated brain region. The most significant point of “Group” × “Time” effect in the activated brain region will be used as the center to construct spherical balls with a radius of 6 mm, and the spherical balls will be regarded as the ROIs. Finally, to obtain the effective connectivity of each patient at different time points, the average time series of all voxels in each ROI will be subjected to dynamic causal model (DCM) analysis.

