**Fig. 2 Fig2:**
[figure not shown]
Bimodal Balance-recovery Model for rTMS protocols in this study. Bimodal Balance-recovery Model for rTMS protocols in this study. cM1, contralesional primary motor cortex; cPMd, contralesional dorsal premotor cortex; rTMS, repeated transcranial magnetic stimulation; RTM, resting motor threshold

If any patients experience headaches, nausea, or changes in their condition throughout the interventions, we will terminate the interventions and provide timely medical assistance. Adverse events will also be reported to the ETHICS committee.

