#### Clinical function assessment and electrophysiological assessment

Clinical function assessment and electrophysiological measurement will be performed at T0, T1, and T2 in Huashan Hospital, Fudan University. The level of motor function will be assessed based on the Brunnstrom stage. Manual muscle test (MMT) and modified Ashworth scale (MAS) will be used to assess muscle strength and muscle tone of the limbs, respectively, whereas the national Institutes of Health Stroke Scale (NIHSS) will be used to assess the severity of neurological deficits in stroke. In addition, Fugl-Meyer Upper Limb Motor Function Rating Scale (FM-UL), Action Research Arm Test Scale (ARAT) and Wolf Motor Function Test Scale (WMFT) will be used to assess the motor function of the affected arm and hand. Activities of daily Living (ADL) will be evaluated using the Modified Barthel Index (MBI).

For electrophysiological evaluation, single-pulse TMS (YRD CCY-4, Yi Ruide Company, Wuhan, China) will be used to assess bilateral hemispherical MEP using a 8-figured coil with an external wing of 7 cm. We will first determine the optimal stimulus point, the location on the scalp with the largest and most consistent MEP in the contralateral Abductor Pollicis Brevis (APB), from which the subsequent neurophysiological assessments will be performed. The resting motor threshold (RMT), which is the minimal stimulus intensity required to evoke MEPs with amplitudes of ≥50 μV in at least five out of 10 consecutive trails, will be determined as the amplitude reference. MEP amplitude and latency, i.e., the peak to peak amplitude and the time period between stimulation onset and start of the largest MEP, will be measured and recorded. In instances where MEP will be recorded in the affected-side APB, it will be denoted as MEP (+), and if multiple measurements fail to yield a MEP, it will be denoted as MEP (−).

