### Statistical analysis

#### Sample size calculation

The sample size for this study was calculated using SPSS 21 software based on a previous study [34]. The mean score of FM-UL assessment in patients who received low-frequency rTMS treatment was 30 at baseline and increased to 43 after intervention, with a common standard deviation of 17. Furthermore, we assumed that the study would have a dropout of 30%, and thus the final target sample size was 60 participants, with 20 assigned to each group when setting a power of 80% and a significance level of 0.05.

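### Intention-to-treat is promised, but the only named comparison is a Group × Time mixed ANOVA that, without imputation, drops every patient missing a visit

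*Protocol article*

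**What the plan says.** Under Group-level analysis the protocol article sets the analysis principle: "The intention-to-treat principle will be used for the analysis of functional and electrophysiological data". For the treatment comparison it then says that "a two-way mixed design ANOVA with between-subject factor “Group” and within-subject factor “Time” will be performed for the clinical and electrophysiological changes", followed by Bonferroni-corrected post hoc comparisons. The software is SPSS 25.0.

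The visits are fixed under Clinical function assessment and electrophysiological assessment: "Clinical function assessment and electrophysiological measurement will be performed at T0, T1, and T2 in Huashan Hospital, Fudan University". T0 has one other named use: "One-way analysis of variance (ANOVA) will be used to compare the demographic characteristics and baseline assessment (T0) of all outcomes among groups". No baseline covariate is named, the levels of Time are not listed, and nothing is said about patients with a missing visit.

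Under Sample size calculation: "we assumed that the study would have a dropout of 30" per cent, giving 20 per group.

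**The concern.** A classical mixed ANOVA needs a value at every level of Time for each patient. Someone assessed at T0 and T1 who misses only T2 leaves the whole analysis, including the comparison at T1, for which the data exist. A set of patients chosen by having completed follow-up is not the set that was randomised. The article therefore names a principle and then a method that does not deliver it unless something is added.

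Two things are at stake. First, if completing follow-up is related to how patients fare, and differently so between arms, the completers' comparison is biased and would still be reported as intention-to-treat. Second, collected information goes unused: T1 values of patients who miss T2, and T0 as a predictor of the later scores.

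**Working it through.** **Inputs from the protocol article.** 60 patients, 20 per arm; 30% dropout; FM-UL 30 rising to 43 (13 points), SD 17; power 80%, significance level 0.05 (two-sided assumed); visits T0, T1, T2.

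**Inputs not given, therefore assumed.** The correlation ρ between visits (0.5 to 0.8), and how many of the lost patients still have T1.

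**1. The plan's own number.** A one-sample (pre–post) normal formula reproduces it:

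n = (17 × (1.960 + 0.842) / 13)² = 13.4, rounded up to 14; 14 / 0.70 = 20 per arm, 60 in total.

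So the plan itself expects 14 completers per arm.

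**2. Patients in the named analysis.** 60 × 0.70 = 42 analysed, 14 per arm; 60 − 42 = 18 randomised patients left out. This holds whether Time has three levels (T0, T1, T2) or two (change scores at T1 and T2), because a missing T2 removes the patient either way.

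**3. Precision at equal numbers.** Per-patient variance is 2σ²(1 − ρ) for change from T0 and σ²(1 − ρ²) with T0 as covariate. The ratio is (1 + ρ)/2. With σ = 17:

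| Assumed ρ | SD of change | SD, T0 as covariate | Variance ratio |
|---|---|---|---|
| 0.5 | 17.0 | 14.7 | 0.75 |
| 0.7 | 13.2 | 12.1 | 0.85 |
| 0.8 | 10.8 | 10.2 | 0.90 |

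**4. Further gain at T1 from patients who miss only T2.** If k of the 6 patients lost per arm have a T1 value, the variance of the T1 contrast is multiplied by about 14/(14 + k): 1.00 for k = 0, 0.82 for k = 3, 0.70 for k = 6. Combined with step 3, the range is 0.75, 0.62 and 0.53 at ρ = 0.5, and 0.90, 0.74 and 0.63 at ρ = 0.8.

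**5. How completers can mislead (a deliberately extreme illustration).** Take no true effect, SD 17, ρ = 0.8 between all visits. In one arm the 30% with the worst T0–T1 change leave before T2; in the other arm the 30% loss is random.

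- The SD of change is 17 × √0.4 = 10.75. The mean of the upper 70% of a standard normal is 0.348/0.70 = 0.497.
- The spurious difference in change from T0 at T1 is 10.75 × 0.497 ≈ 5.3 points. At T2 it is half of that, about 2.7, because the two changes correlate at 0.5.
- These are differences in change. The differences in raw score are 17 × √0.1 × 0.497 ≈ 2.7 at T1 and 0 at T2.
- A likelihood analysis using all T0 and T1 data gave about zero at both visits in simulation, since loss here depends only on observed values.

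**The case against.** The strongest reply is that exclusion of incomplete patients is inferred. The article does not say completers only, and imputation followed by mixed ANOVA would satisfy both sentences. A missing-data rule is commonly left to a statistical analysis plan, which is not shown. That stands in part: the absence of such a rule is no finding, and a definite breach of intention-to-treat cannot be asserted. What remains is that the article fixes a model which, as named, does not carry out the stated principle.

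Several stronger readings are tempting, and the document does not support them.

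- **That T0 is certainly a level of Time.** It is the natural reading, with three visits and no covariate. But the ANOVA "will be performed for the clinical and electrophysiological changes", which could mean change scores.
- **That dropout leaves the trial below its planned size.** It does not; 14 per arm is the number the 30% allowance was built on.
- **That T0 handling costs much power.** With an assumed 6.5-point advantage and ρ = 0.8, simulation gives 35% for Group × Time against 44% for a baseline-adjusted T1 contrast. But that sets 14 per arm against an assumed 17. At equal numbers it is about 34% against 36%. With Bonferroni correction for three pairs, the contrast on 17 per arm falls to 27% (15% at ρ = 0.6, against about 18% for the interaction). The low power of the Group main effect is also beside the point, because the article does not name it as the efficacy test.
- **That patients whose stimulation is stopped are lost.** For headache, nausea or a change in condition the article says "we will terminate the interventions and provide timely medical assistance". That ends treatment, not assessment, and Outcome measures has all patients assessed at all time points.
- **That intention-to-treat is breached for rs-fMRI and DTI.** The promise covers functional and electrophysiological data only.

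**Conclusion.** The point holds as a mismatch between the stated principle and the named method. Without imputation, about 18 of 60 randomised patients would be left out of an analysis described as intention-to-treat. The main consequence is exposure to selection bias; its size cannot be read from the protocol, and the 5.3-point figure only shows the mechanism under an extreme assumption. The second consequence is avoidable imprecision. The T1 contrast could have 0.75 to 0.90 of the variance of a change-score contrast at equal numbers for ρ of 0.5 to 0.8, and less again if some lost patients have T1. That gain is modest at high correlation. Both ρ and the timing of dropout are assumptions.

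**What to change.** Under Group-level analysis, for the clinical and electrophysiological outcomes, replace the mixed ANOVA by a likelihood-based linear mixed model in SPSS:

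- outcomes: the values at T1 and T2;
- fixed effects: arm, visit and arm × visit, with the T0 value of the same outcome as covariate;
- patients: all randomised patients with at least one post-baseline value, in their assigned arm;
- report: the arm contrasts at T1 and T2, with the Bonferroni correction already planned.

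State that the model assumes values are missing at random. Patients with T0 only still do not enter; they would add almost nothing under either model. If the mixed ANOVA is kept, the text must say how missing visits are imputed and which levels Time has.

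The cost is analysis wording and a little more analysis work, with the same data and software. No change to sample size or visits is needed.

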## Abstract

**Background:**

Previous studies have revealed that low frequency repeated transcranial magnetic stimulation (rTMS) on the contralesional primary motor cortex (cM1) is less effective in severe stroke patients with poor neural structural reserve than in patients with highly reserved descending motor pathway. This may be attributed to the fact that secondary motor cortex, especially contralesional dorsal premotor cortex (cPMd), might play an important compensatory role in the motor function recovery of severely affected upper extremity. The main purpose of this study is to compare the effectiveness of low frequency rTMS on cM1 and high frequency rTMS on cPMd in subcortical chronic stroke patients with severe hemiplegia. By longitudinal analysis of multimodal neuroimaging data, we hope to elucidate the possible mechanism of brain reorganization following different treatment regimens of rTMS therapy, and to determine the cut-off of stimulation strategy selection based on the degree of neural structural reserve.

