The interhemispheric inhibition (IHI) model, which is commonly used as the fundamental theory for standardized rTMS treatment, was first proposed by Murase in 2004 [22], which suggests that the bilateral primary motor cortexes (M1) are connected through the corpus callosum in a balance of competing inhibition in healthy individuals. However, the IHI balance is disturbed after the onset of stroke, thereby leading to over activation of the contralesional hemisphere. Specifically, damage to the affect hemisphere weakens its inhibitory effect on the contralesional hemisphere, ultimately resulting in abnormally increased excitability of cM1. Notably, the over activation of cM1 will in turn inhibit the affect M1, causing a vicious circle. The disrupted balance between bilateral M1 will eventually hinder the motor output and impede the recovery of upper limb motor function in stroke survivors. Ideally, according to the standardized treatment protocol [19, 20], high-frequency rTMS is able to increase the excitability of affected M1, whereas low-frequency rTMS is capable of reducing the excitability of cM1, thereby enabling the disrupted IHI to reach a new equilibrium. However, some studies have found that the standardized rTMS protocol is not suitable for all stroke patients [11, 12]. It is worth noting that patients with severe hemiplegia seem to be less suitable for this standardized rTMS protocol [19]. This has led to some researchers questioning the value of classic IHI imbalance theory in clinical practice. Pino et al. [23] proposed the bimodal balance-recovery model in stroke recovery, which suggests that determining the mode of recovery to be adopted depends on the degree of damage to the affected hemisphere, namely structural reserve. For example, in patients with less damage (higher structural reserve), the classic IHI imbalance mode will dominate the recovery process, and the increased activation of contralesional hemisphere will not be conducive to motor recovery. In such cases, standardized low frequency rTMS of cM1 can exert therapeutic effects by inhibiting this abnormal excitability. In contrast, for patients with low structure reverse, the recovery process will be dominated by the compensatory mode because the increased motor cortex excitability on the unaffected side will be conducive to rehabilitation. In this case, the standardized low-frequency rTMS protocol might not be effective, and thus applying high-frequency rTMS on cM1 is a better option. Taking these two recovery models together, we believe that if we can identify the cut-off of structural reserve, we might be able to evaluate the real effects (inhibitory or compensatory) of the contralesional hemisphere on motor output. This will aid in selecting the optimum rTMS stimulation strategy on contralesional hemisphere (low frequency or high frequency).

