### Outcome measures

All patients will receive clinical function assessment, electrophysiological measurement, and multimodal fMRI scanning at all time points. Healthy subjects will only receive fMRI scanning scan at T0. The outcome measure timing is listed in Table 2.

**Table 2 Tab2:** Outcome measure timing

Groups	cM1-LF, cPMd-HF & CON group			HC group		
Time point	T0	T1	T2	T0	T1	T2
Clinical function assessment	○	○	○			
Electrophysiological assessment (MEPs, RMT)	○	○	○			
MRI scan	○	○	○	○		

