#### DTI

The bilateral posterior limb of internal capsule (PLIC), bilateral cerebral peduncle, and corpus callosum of each patient will be delineated manually by two radiologists. For each patient, the common part of the results recorded by the two radiologists will be adopted as the regions of interest (ROIs). The mean fractional anisotropy (FA) will be calculated with all the ROIs for each hemisphere. Notably, FA asymmetery index (FA AI) is defined by the following formula:

$$FA\ AI=\frac{\left({FA}_c-{FA}_a\right)}{\left({FA}_c+{FA}_a\right)}$$where FAc is the FA of the contralesional hemisphere and FAa is the FA of the affected hemisphere. FA AI can be used to quantitatively evaluate the structural integrity of CST and corpus callosum.

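### T0 structural reserve, which the protocol treats as governing recovery and response to rTMS, is measured in every patient but left out of the clinical treatment model; the gain from adjusting is of unknown size but cheap to secure

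*Protocol article*

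**What the plan says.** The Background adopts a model of stroke recovery in which "determining the mode of recovery to be adopted depends on the degree of damage to the affected hemisphere, namely structural reserve". The Abstract adds that low-frequency cM1 stimulation "is less effective in severe stroke patients with poor neural structural reserve than in patients with highly reserved descending motor pathway". Aims and hypotheses then rests the choice between high and low frequency on a reserve cut-off.

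Reserve is measured at baseline. Under Outcome measures, "All patients will receive clinical function assessment, electrophysiological measurement, and multimodal fMRI scanning at all time points". The DTI section states that "FA AI can be used to quantitatively evaluate the structural integrity of CST and corpus callosum". The electrophysiological section also gives a binary marker: "In instances where MEP will be recorded in the affected-side APB, it will be denoted as MEP" (+), and otherwise MEP (−).

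Under Group-level analysis, the model for the clinical scales has two factors: "a two-way mixed design ANOVA with between-subject factor “Group” and within-subject factor “Time” will be performed for the clinical and electrophysiological changes". FA AI appears there only as an outcome, in the list "including Eg, El, network betweenness, clustering coefficient, and FA AI". Baseline values are handled by a test: "One-way analysis of variance (ANOVA) will be used to compare the demographic characteristics and baseline assessment (T0) of all outcomes among groups". No adjustment follows from it. The Correlation analysis section relates MRI and electrophysiology to clinical scores in the two active arms only. Randomization and grouping describes 20 per arm and no balancing on reserve.

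**The concern.** The protocol names one baseline characteristic as the main driver of outcome and collects it in all patients, yet does not use it in comparing the arms. Two things follow. Any variation in FM-UL change that reserve explains stays in the error term. And if the arms happen to differ in reserve at T0, nothing in the model corrects for it. The T0 one-way ANOVA may reveal the imbalance, but the plan gives no consequence. With 20 per arm, and fewer after the 30% dropout that the protocol assumes, neither is negligible if reserve is as important as the protocol believes.

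**Working it through.** **The protocol's own figure.** Inputs from Sample size calculation: FM-UL 30 rising to 43 (13 points), SD 17, power 80%, significance 0.05 (two-sided assumed), dropout 30%. The stated 20 per group is matched by a one-sample (pre-post) normal formula: (17 × (1.960 + 0.842) / 13)² = 13.4, so 14; 14 / 0.7 = 20. The 13 is thus a change within one arm. Below it is borrowed as a between-arm difference, which is an assumption.

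**Which variance matters.** The model includes T0, so the treatment effect is the Group × Time term, and any effect of reserve that is constant over time cancels. What counts is the correlation ρ of T0 reserve with *change*, and the SD of change, S = 17 × √(2(1 − r)), where r is the T0-to-follow-up correlation of FM-UL. The document gives neither ρ nor r.

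**Power.** Two arms of n = 20, two-sided 0.05, noncentral t with noncentrality 13 / (S√(1 − ρ²)) × √(n/2), and 2n − 2 degrees of freedom, less one when the covariate is used:

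| r (assumed) | S | unadjusted | ρ = 0.3 | ρ = 0.5 |
|---|---|---|---|---|
| 0.5 | 17.0 | 65% | 70% | 78% |
| 0.7 | 13.2 | 86% | 89% | 94% |
| 0.8 | 10.8 | 96% | 97% | 99% |

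For example, at r = 0.5 without adjustment, 13/17 × √10 = 2.42, which gives 65%. With 14 completers per arm and r = 0.5, power is 50% unadjusted against 53% (ρ = 0.3) and 61% (ρ = 0.5). These figures are for one pair of arms, before the planned Bonferroni correction.

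**Chance imbalance.** For a standardised covariate, the SD of the difference between two arm means is √(2/20) = 0.316. The probability of a difference of at least 0.5 SD is 2 × (1 − Φ(0.5/0.316)) = 11%. At 14 per arm it is 19%. For at least one of the three pairs it is about 25% and 38%.

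**What an imbalance does.** If the standardised slopes of change on reserve are b₁ and b₂ in the two arms, an imbalance of 0.5 SD moves the contrast on average by 0.5 × S × (b₁ + b₂)/2.
- Common slope 0.3 to 0.5: 2.6 to 4.3 points at S = 17, and 1.6 to 2.7 points at S = 10.8.
- Same direction but unequal, for example 0.5 and 0.2 at S = 17: 0.5 × 17 × 0.35 = 3.0 points.
- Equal and opposite slopes: zero.

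**Simulation, common slope, no treatment effect, three arms of 20.** Overall type I error was about 5% with or without the covariate. Among trials where some pair differed by more than 0.5 SD, the unadjusted error was about 5% (ρ = 0.3) and 11% (ρ = 0.5), against about 5% adjusted.

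**Simulation, equal and opposite slopes in the two active arms.** A main-effect covariate gained nothing: the standard error of the contrast went from 0.315 to 0.318.

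**The case against.** The strongest objection is that the protocol's mechanism is effect modification. If higher reserve favours cM1-LF and lower reserve favours cPMd-HF, with slopes of opposite sign, an imbalance need not shift the contrast between them, and a single common slope does not help. The arithmetic above confirms this for equal and opposite slopes. The objection does not dispose of the point: where reserve acts in the same direction in the arms, even unequally, a shift occurs, adjustment removes it, and the standard error falls. It does mean that a common slope alone would not match the protocol's reasoning.

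Other objections stand in part:
- Randomisation keeps the unadjusted comparison unbiased. A reader might infer that it is invalid or systematically biased, or that a material imbalance is likely. The document supports neither: overall error is about 5%, and 11% for two given arms is a risk, not an expectation.
- A reader might take it as established that reserve determines outcome. The Background reports a proposed model and gives no correlation. Eligibility limited to subcortical stroke with Brunnstrom hand stage IV or below may narrow the range of reserve, although the planned search for a cut-off presumes useful variation.
- Patients without usable T0 DTI could be dropped, against the intention-to-treat statement. The fix has to prevent that.
- Covariates are often left to an analysis plan. Here, however, the article states the model and its factors, so the point concerns a stated choice. The planned joint analysis of imaging and function serves the cut-off question and does not adjust the arm comparison.

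**Conclusion.** The point holds as one of efficiency and of robustness to chance imbalance, not of validity. The stated model omits a baseline measure that the protocol itself treats as central and already collects. How much this costs is unknown. Over the assumed range ρ = 0.3 to 0.5, the gain in pairwise power at 20 per arm runs from about 4 to 12 percentage points if r = 0.5, down to about 1 to 3 points if r = 0.8. Reading the larger gains as the cost of the omission is tempting but unsupported, since they require r to be near 0.5. The shift from a 0.5 SD imbalance is 1.6 to 4.3 points over the same range, against 13, and only if reserve acts in a common direction across arms. All figures also rest on using the within-arm 13 as a between-arm difference and 17 as the SD at each time point.

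**What to change.** In the Group-level analysis model for FM-UL and the other clinical scales:

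1. Prespecify T0 FA AI of the corticospinal regions (posterior limb of the internal capsule and cerebral peduncle), mean-centred, as a covariate with a reserve × Time term. A covariate that is constant over time would leave the Group × Time contrast unchanged. Name the regions, because the DTI section also includes the corpus callosum.
2. Report adjusted and unadjusted arm differences side by side.
3. Add a secondary Group × reserve × Time term, since the protocol posits effect modification that a common slope does not capture.
4. Fix the covariate before unblinding. Impute missing T0 FA AI, for example by the overall mean with a missing indicator, so that no randomised patient is dropped. Do not switch to MEP status after seeing the data.

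The cost is a few sentences and one or a few degrees of freedom (about 0.1 point of power at 20 per arm for a single covariate that proves uninformative), with no new data. There is little or no gain if reserve is not prognostic, or if it acts in opposite directions in the two active arms.

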### Randomization and grouping

The 60 eligible stroke patients will be randomly assigned to three groups with 20 patients in each group: low-frequency rTMS of cM1 (cM1-LF) group, high-frequency rTMS of cPMd (cPMd-HF) group, and sham-stimulation control (CON) group. The random sequence will be created using STATA 12.0 software (StataCorp, Texas, USA) by a professional third-party statistician from Fudan University. The randomization list will only be known by this research coordinator and will be concealed from other study personnel. However, the research coordinator will not participate in recruitment, subsequent intervention and assessment, and final data analysis. In addition, 20 healthy people will be recruited into the healthy control (HC) group. The HC group will be matched with stroke groups in terms of age, gender, and education.

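### Bonferroni is valid but needlessly conservative for the three pairwise arm comparisons; a three-arm step-down at a fixed time point keeps 5% family-wise error and has more power

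*Protocol article*

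**What the plan says.** The abstract of the protocol article gives the main purpose as to "compare the effectiveness of low frequency rTMS on cM1 and high frequency rTMS on cPMd". Under Randomization and grouping, patients are "randomly assigned to three groups with 20 patients in each group", so there are three pairs of arms and the main question is one of them. Assessments are at T0, T1 and T2.

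Under Group-level analysis, "a two-way mixed design ANOVA with between-subject factor “Group” and within-subject factor “Time” will be performed for the clinical and electrophysiological changes". The text then says that "Bonferroni correction will be employed for post hoc multiple comparisons", and a P value below "0.05 will be considered statistically significant for all analyses". It does not say which comparisons form the Bonferroni family: the three arm pairs, the arm pairs at each time point, or pairs of time points as well. It names no step-down or closed procedure.

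Under Sample size calculation, the FM-UL mean in a low-frequency group "was 30 at baseline and increased to 43 after intervention", "with a common standard deviation of 17". With 30% dropout this leads to 60 patients, "with 20 assigned to each group when setting a power of 80% and a significance level of 0.05". No allowance for a Bonferroni correction is mentioned.

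**The concern.** With three arms, the pairwise null hypotheses are logically linked: if any two are true, so is the third. The number of true pairwise nulls is therefore three, one or none, never two. Plain Bonferroni ignores this and holds every pair to 0.05/3 = 0.0167, even after one difference has been established and at most one null can remain true.

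The trial is small, and its main comparison bears the correction. If a method with the same 5% family-wise guarantee detects more, the power given up is avoidable.

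**Working it through.** **The plan's own figure.** The stated 20 per arm comes back from a within-group (paired) normal calculation, two-sided 0.05, 80% power:

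n = (17 × (1.960 + 0.842) / 13)² = 13.4, so 14; 14 / 0.70 = 20 per arm, 60 in total.

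The same inputs used for a difference between two arms give 27 per arm, or 39 after dropout. The expected completers are thus 14 per arm, and 20 is the best case.

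**Per-pair power at fixed levels.** Normal approximation for a between-arm difference of 13 with SD 17 (the use as a between-arm effect is an assumption):

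| Per arm | level 0.05 | level 0.0167 |
|---|---|---|
| 14 | 53% | 36% |
| 20 | 68% | 51% |

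**Why the Shaffer step-down controls the error at one time point.**
- All three nulls true: an error requires the smallest p to be at or below 0.05/3, which has probability at most 3 × 0.05/3 = 5%.
- Exactly one null true: it is never tested above 0.05, so the error is at most 5%.
- Exactly two nulls true cannot occur.

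If Bonferroni rejects any pair, the smallest p is at or below 0.05/3, the first step is passed, and the other pairs face 0.05 instead of 0.0167. Shaffer therefore rejects at least as much as Bonferroni in every data set.

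**Simulated power.** 200,000 runs per setting, three normal arms measured once, SD 17, pooled-variance t tests. Closed F means a three-group F test at 0.05, then each pair at 0.05. Power for cPMd-HF versus cM1-LF when cPMd-HF is 13 points above two equal arms:

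| Per arm | Bonferroni | Holm | Shaffer | Closed F |
|---|---|---|---|---|
| 14 | 33% | 35% | 39% | 42% |
| 20 | 49% | 52% | 56% | 59% |

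If cM1-LF instead lies halfway between sham and cPMd-HF (a difference of 6.5 for the main pair), Bonferroni, Shaffer and closed F give 8%, 13% and 14% with 14 per arm, and 11%, 19% and 20% with 20 per arm.

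**Simulated family-wise error.**

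| Truth | Bonferroni | Shaffer | Closed F |
|---|---|---|---|
| All arms equal | 4.3% | 4.3% | 4.9–5.0% |
| Two equal, third far away | 1.6–1.7% | 5.0% | 5.0% |

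**What changes with two follow-up times.** The argument above covers three means at one time. A Group-by-Time test can be significant because of T1 alone. With one arm different at T1 only, an assumed within-patient correlation of 0.6, a Group-by-Time gate at 0.05 and then each pair at 0.05 (20,000 runs per setting), at least one false T2 arm difference occurred in:
- 8% of runs with 14 per arm and 10% with 20 per arm, for a T1 effect of 13/17 = 0.765 SD;
- 12% for a T1 effect of 1.5 SD.

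Dividing by 3 behind the same gate gave 3–4%.

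**The case against.** The strongest reply is that Bonferroni is valid, conventional and easy to report, so nothing here is an error. That stands: the point is efficiency. Bonferroni also has real side benefits. It gives simple simultaneous confidence intervals. Its realised error is lower, and it holds the expected number of false rejections at 5% when all arms are equal, against 6.2–6.4% for Shaffer and about 7.5% for closed F.

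The second reply is that the plan states neither a divisor nor a family, and a fuller document may do so. This also stands, and the division by 3 is labelled an inference throughout.

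The third reply is the most important. A reader might infer that the correction buys no protection at all, so that each pair can be tested at 0.05 once the planned Group-by-Time test is significant. The documents do not support that. With assessments at T0, T1 and T2, the post hoc family may include arm pairs at two follow-up times, and the 8–12% above is the result. The gain exists only within a fixed time point or a fixed change.

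Finally, closed F does not dominate an ungated Bonferroni in every data set: it missed a Bonferroni-significant pair in at most 0.5% of runs. Shaffer has no such exception.

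**Conclusion.** The point holds as an avoidable loss of efficiency in a stated method. For the three arm pairs at one prespecified time point or change, the gain on the main comparison is about 6 points (Shaffer) or 9 points (closed F) with 14 per arm, and about 7 or 10 points with 20, with family-wise error at or below 5%.

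The gain rests on three assumptions: that the Bonferroni family is the three arm pairs; that the 13-point within-group change and SD 17 can stand for a between-arm difference; and that cM1-LF equals sham. Under the halfway pattern the gain is about 5 to 9 points.

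A reader might also infer that the change repairs the power of the trial. It does not: the main comparison stays at 42–59% under the favourable pattern, because the sample size reproduces from a within-group change.

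**What to change.** Under Group-level analysis, replace the Bonferroni sentence for the arm comparisons by wording such as:

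> For each outcome, the three pairwise arm comparisons of the change from T0 to [one prespecified time point] are tested by the Shaffer step-down: the smallest p value at 0.05/3 and, if significant, the other two at 0.05 each.

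An equivalent option is a three-group F test of that same change at 0.05, followed by each pair at 0.05.

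If arm pairs are tested at both T1 and T2, either:
- run the procedure separately at each time point with its own first step, which controls error at 5% per time point (at most 2 × 5% = 10% over both); or
- use Holm over the full arm-by-time family of six pairs, starting at 0.05/6 = 0.0083, for 5% overall.

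Do not use one Group-by-Time test as the gate for unadjusted pairs. Keep a correction for any comparisons between time points, and state the family explicitly.

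The cost is a few sentences, no patients, and the loss of simple simultaneous intervals; ordinary 95% intervals can be reported if labelled as unadjusted.
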